#### Preparation period

When the participant is diagnosed with at least probable sarcopenia based on the EWGSOP2-defined low muscle strength and meets the inclusion criteria, the participant is eligible for both the cross-sectional phase and the longitudinal phase of TEMPUS-FUGIT.

For the longitudinal phase, the sarcopenic participants will be 1:1 block randomized into one of the five intervention groups, as previously described by Dedeyne et al. [29]. All these participants will be requested to take 800 International Units (IU) of vitamin D and one capsule of omega-3 PUFA/placebo per day, starting one month before the baseline test visit. Participants will also be asked to keep a food diary during four non-consecutive days in order to individually supplement protein intake until the recommended daily allowance (RDA) for older adults with chronic conditions (i.e., 1.5 g/kg BW/day) [35]. Furthermore, these food diaries will be analyzed to obtain the participants’ habitual protein and energy intake, and to assess possible associations with GM composition. Five days prior to the baseline test visit, participants will be requested to start to take their individualized protein supplements or placebo powder and will wear an inertial measurement unit (IMU) (MoveMonitor + , McRoberts, The Netherlands) to monitor physical activity. Participants will be requested to register the intake of the vitamin D, omega-3/placebo and protein/placebo supplement in a trial diary during the intervention. In the week prior to the baseline test visit, participants need to collect two fecal samples produced at two separate moments with the provided material (Laboratory of Molecular Bacteriology, KU Leuven/Rega Instituut, Vlaams Instituut voor Biotechnologie (VIB), Belgium). Immediately after sample collection, the participant fills out the Bristol Stool Score Chart [36] to determine fecal consistency and preserves the samples at -20°C [37]. Finally, participants will be requested to complete a general health questionnaire as well as the ROME IV questionnaire to screen for IBS symptoms [38].

When the participant does not meet the EWGSOP2-criteria for (probable) sarcopenia, the participant will be included as a non-sarcopenic control person in the cross-sectional phase of the TEMPUS-FUGIT study. Non-sarcopenic participants will follow the same preparation period as described above, being requested to complete food diaries and health questionnaires, to collect two stool samples and wear the IMU, but without being block randomized to the interventions (nutritional supplementations and/or the exercise program).

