#### Baseline test visit

For both the non-sarcopenic controls and the sarcopenic participants, a test visit at the study center will follow the preparation period. During this visit, the four-day food diary, the IMU and the two frozen fecal samples brought along by the participant (avoiding thawing using ice packs) will be collected and fasted blood samples will be taken.The fecal samples will immediately be stored at -80 °C until analysis of intestinal inflammatory markers (fecal calprotectin, lactoferrin and S100A12) and GM composition. Quantitative Microbiome Profiles (QMP) will be obtained through the following extensive -omics analysis. Targeted (16S/18S) amplicon sequencing analysis of the V3-V4 variable region of the 16S rRNA gene, via reverse polymerase chain reaction (RT-qPCR) technique will provide information about GM taxonomic composition, i.e., the type of GM present, and their abundance.. Metagenomic analysis (comprehensive assessment of DNA of the complete content of a clinical sample) will be performed through whole genome shotgun analysis using next generation platforms. Intestinal inflammatory markers will be determined through Enzyme Linked Immunosorbent Assay (ELISA).In fasted blood samples, the following parameters will be determined: systemic inflammatory parameters (hs-CRP, IL-4, IL-6, IL-13, IL-1β, TNF-α and creatine kinase), muscle markers (myostatin, activin A, irisin, apelin), clinical parameters (hemoglobin, eGFR, serum albumin, fasting glucose, red blood cell count, hematocrit, Mean Corpuscular Volume (MCV), Mean Corpuscular Hemoglobin (MCH), Mean Corpuscular Hemoglobin Concentration (MCHC), white blood cell count and formula, platelet count, hemoglobin A1c (HbA1c), ferritin, aspartate aminotransferase (AST), alanin transaminase (ALT), γ-glutamyltransferase, total and direct bilirubin, total protein, serum protein electrophoresis, uric acid, sedimentation rate, triglycerides and total, high-density lipoprotein (HDL) and low-density lipoprotein (LDL) cholesterol, and hormonal status (25-hydroxyvitamin D, vitamin B12, morning cortisol, insulin, insulin-like growth factor (IGF-1)).

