#### Intervention period

In the longitudinal RCT phase of the TEMPUS-FUGIT study, sarcopenic older adults will be block randomized to one of five interventional programs, stratified according to sex, via a sealed opaque envelope by an independent researcher. Participants in each of the interventional groups will follow a 12-week intervention period as previously described [29]. Briefly, the interventions consist of a training program and/or nutritional supplementation. The exercise intervention comprises an adapted version of the home-based Otago exercise program (OEP) consisting of warming-up, balance, strength and stretching exercises together with a walking program. The OEP has been proven to effectively reduce falls in older community-dwelling adults. Currently the OEP is being investigated in the context of sarcopenia, reporting a preliminary beneficial effect [50, 51]. The protein intervention consists of a personalized amount of protein supplementation, rich in leucine (Resource instant protein, Nestlé), aiming to reach the RDA of 1.5 g/ kg BW/day, spread equally over the day [35]. The placebo protein is isocaloric digestible maltodextrin (Resource dextrin maltose, Nestlé). Omega-3 PUFA supplements consist of 450 mg docosahexanoic acid (DHA) and 500 mg of eicosapentanoic acid (EPA) per day. The omega-3 PUFA placebo contains 1 g peanut oil. All groups receive vitamin D supplementation (800 IU cholecalciferol). Researchers and participants will be blinded to the nutritional supplements, but not to the exercise program. The statistician is blinded to all the interventions. At each contact moment during the intervention, researchers encourage participants to comply to the interventions. An overview of the study design/ intervention groups is given in Fig. 3.

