### Outcome measurements

For the cross-sectional phase, outcome measurements will be taken at the baseline test visit.The primary outcomes in this phase are:Differences in multiple GM α-, and β-diversity indices, enterotypes, bacterial cell counts and abundance of specific taxa between sarcopenic older adults and non-sarcopenic controls using two fecal samples collected in each group at the baseline test visit [52, 53]. Both GM diversity indices and measures for expression of bacterial abundance will be specified in the section “Assessment of GM composition and statistical analyses” further below.Differences in the levels of the intestinal inflammatory markers fecal calprotectin, lactoferrin and S100A12 between sarcopenic older adults and non-sarcopenic controls using two fecal samples collected in each group at the baseline test visit.Secondary outcomes assessed in sarcopenic older adults are:Associations between GM composition and clinical parameters: 1) ALM (by whole body DXA and BIA), muscle strength (HGS, CST and knee strength) and physical performance (gait speed and SPPB); 2) protein intake by four-day food diaries and risk of malnutrition by the MNA-SF.Associations between GM and levels of systemic (hs-CRP; IL4, IL6, IL-13, IL-1β, TNF-α, and creatin kinase) and intestinal (fecal calprotectin, lactoferrin and S100A12) inflammatory markers.Associations between levels of systemic and intestinal inflammatory markers.Associations between fecal calprotectin, lactoferrin, S100 and respectively: 1) aforementioned systemic inflammatory markers; 2) ALM (whole-body DXA), muscle strength (HGS, CST, knee strength) and physical performance (gait speed, SPPB); 3) systemic muscle biomarkers (myostatin, activin A, irisin, apelin).

For the longitudinal phase in sarcopenic participants, outcome measurements will be collected from the baseline test visit until the week 12 visit. The primary outcome of this phase is:Change in GM composition between the protein intervention group (group B, Fig. 3) and the placebo group (group E).

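### The baseline stool samples of sarcopenic participants are taken after trial supplements have started, so the case–control contrast is confounded by supplementation and the omega-3 contrasts in the RCT start from an on-treatment baseline

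*Protocol article*

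**What the plan says.** All places are in the protocol article.

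- **Preparation period, sarcopenic participants.** They are randomised in this period. All take "vitamin D and one capsule of omega-3 PUFA/placebo per day, starting one month before the baseline test visit". The powder follows: "Five days prior to the baseline test visit, participants will be requested to start to take their individualized protein supplements or placebo powder". Stool collection overlaps with it: "In the week prior to the baseline test visit, participants need to collect two fecal samples produced at two separate moments".
- **Preparation period, controls.** They follow the same preparation, "but without being block randomized to the interventions (nutritional supplementations and/or the exercise program".
- **Baseline test visit.** At this visit "the two frozen fecal samples brought along by the participant (avoiding thawing using ice packs) will be collected and fasted blood samples will be taken".
- **Intervention period and Table 1.** Every arm receives vitamin D. The capsule placebo is peanut oil and the powder placebo is digestible maltodextrin. Further stool samples come at weeks 4, 8 and 12. None is scheduled before supplementation.
- **Outcome measurements.** The two baseline stool samples carry the primary cross-sectional comparison of GM and fecal calprotectin, lactoferrin and S100A12. For the RCT, "outcome measurements will be collected from the baseline test visit until the week 12 visit", and the primary outcome is change in GM composition, group B (protein) against group E (placebo).

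**The concern.** The same two samples serve two purposes, and each needs a sample untouched by the trial.

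In the case–control phase, being a case means having taken trial supplements for about a month, and being a control means having been assigned none. A difference in GM or fecal markers could come from sarcopenia, from the supplements, or from both. Matching on gender, age and BMI, and regression adjusted for confounders such as age, do not address this exposure. The Background hypothesises that the anabolic interventions change GM in sarcopenic persons, so the protocol cannot treat active omega-3 and protein as inert. The limitations in the Discussion do not mention the exposure.

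In the RCT, any effect already present in the starting sample is subtracted from, or adjusted out of, the change being tested. The baseline associations within cases (GM with inflammatory markers, strength, muscle mass and intake) are measured after the arms have begun to differ.

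**Working it through.** **No stated figure to reproduce.** The point rests on the order of events. The article gives no power, effect size or standard deviation, so every effect share below is an illustration under a stated assumption.

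**Timeline, with the baseline visit as day 0 and one month taken as 30 days**

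| Event | Cases | Controls |
|---|---|---|
| Vitamin D and omega-3 or peanut-oil capsule start | day −30 | not assigned |
| Protein or maltodextrin powder starts | day −5 | not assigned |
| Two stool samples | day −7 to 0 | same week |
| Fasted blood | day 0 | day 0 |
| Later stool | weeks 4, 8, 12 | none |

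Exposure at stool sampling in cases:
- Vitamin D and capsule: 30 − 7 = 23 days up to 30 days.
- Powder: none for stool on days −7 to −5, and up to 5 days otherwise.

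**Case–control comparison.** By assignment, 100% of cases and 0% of controls are on vitamin D plus a capsule. To show the sensitivity, assume supplements shift a marker by 0.2 or 0.3 SD and sarcopenia has no effect. With 100 per group and two-sided 0.05, a two-sample comparison gives p ≤ 0.05 in about 29% or 56% of trials respectively, instead of 5%.

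**RCT, contrasts involving omega-3.** At week 12 the capsule has been taken for 30 + 84 = 114 days. The share of the total effect already present at baseline is:
- Linear build-up: 23/114 = 20% to 30/114 = 26%. Counting 84 days from the sample rather than from the visit makes the lower end 23/107 = 21%.
- Saturating build-up, E(t) = 1 − 2^(−t/h), share = E(t)/E(114): with h = 28 days, 46% to 56%; with h = 14 days, 68% to 78%; with h = 2 days, about 100%.

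**RCT, primary contrast B against E.** Vitamin D is common to both arms. On the labels in Outcome measurements the two groups differ in the powder only. At week 12 the powder has been taken for 5 + 84 = 89 days.
- If both stools precede the powder, the share is 0.
- If samples fall evenly over the 7 days, 5/7 = 71% follow the start, with 2.5 days of powder on average. Linear build-up then gives 5/7 × 2.5/89 = 2.0%.
- A sample on day 0 gives at most 5/89 = 5.6% under linear build-up.
- Saturating build-up, averaged over the same even spread: 5% (h = 28 days), 8% (h = 14), 15% (h = 7), 38% (h = 2).

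**Would dropping the baseline be better?** Take a single follow-up, with correlation ρ between baseline and follow-up. Adjusting for baseline multiplies the variance by 1 − ρ². Omitting it therefore costs 1/(1 − 0.7²) = 1.96 times the sample size at an assumed ρ = 0.7, and 1/(1 − 0.5²) = 1.33 times at ρ = 0.5. If a share p of the effect is already in the baseline, the adjusted analysis keeps 1 − ρp of it. Omission gains power only when (1 − ρp)² < 1 − ρ², that is, p > 0.41 at ρ = 0.7 or p > 0.27 at ρ = 0.5. The linear shares above, at most 26%, stay below both limits.

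**The case against.** Several points on the other side stand.

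- **Which exposure is certain.** Vitamin D is the only active supplement that every case is sure to take. The Background hypothesis concerns the anabolic interventions, not vitamin D or placebos. The Discussion argues that digestible maltodextrin does not reach the colon. The share of cases on active omega-3 or protein depends on Fig. 3, which was not available in the text reviewed. A reader might infer that sarcopenia is wholly inseparable from active treatment, but the article does not support that. Cases on placebo supplements offer a partial separation, although vitamin D, peanut oil and maltodextrin remain. Assigning controls nothing also does not mean that they take nothing of their own.
- **The primary RCT contrast.** A reader might infer that every baseline sample is weeks into treatment for B against E as well, or that the trial would need 1.5 to 4.6 times as many participants. The first fails because the month of exposure concerns the capsule and vitamin D, and stool on days −7 to −5 precedes the powder. The second assumes that 25% to 75% of the 12-week protein effect is present after at most five days of powder, which leaves out every slow build-up.
- **The analysis model.** The article names linear mixed models. How the baseline enters them is normally left to the analysis plan.
- **Associations within cases.** Arm is randomised, so it is independent of pre-existing strength and muscle mass. For those associations it mainly adds noise. It could still link GM and inflammatory markers if a supplement moves both.
- **Character of the study.** It is declared exploratory, with about 100/5 = 20 participants per arm, and enrolment began in 2021.

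None of this alters the order of events or the fact that cases and controls differ in assigned supplementation.

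**Conclusion.** The concern holds, and is strongest for the cross-sectional phase. Its primary comparison of GM and fecal markers is confounded by trial supplementation, fixed by design in all cases and no controls, and the planned matching cannot remove it. The size of the bias cannot be computed from the article.

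For the RCT the conclusion is narrower. Contrasts involving omega-3 use an on-treatment baseline, with about 20–26% of the total effect already present under linear build-up and more if it saturates early. For B against E, dilution is possible but may be nil or about 2%; it becomes material only if protein changes GM within days. Vitamin D cannot dilute any contrast between arms. These shares rest on a 30-day month, even sampling over the week (for the averaged powder figures) and assumed build-up curves. No sample-size inflation can be stated as fact. Because randomisation precedes the supplements, comparisons of later levels between arms that do not use the baseline sample are not diluted.

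**What to change.** **Going forward.** Reconcile Preparation period and Outcome measurements by scheduling both baseline stool samples of cases before the first capsule, with the same window after screening for controls. The supplement schedule stays as it is. Use these samples for the case–control comparison and as the RCT baseline. A pre-supplement blood tube for inflammatory markers is optional: the screening draw takes place only when no recent laboratory results exist, so it would be an extra draw for some.

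**Participants already enrolled.**
1. Add randomised arm as a covariate in the within-case association models.
2. Report the case–control comparison also in cases allocated to placebo supplements, noting that vitamin D, peanut oil and maltodextrin remain.
3. Report comparisons between arms of week 4–12 levels, not adjusted for the on-supplement sample, as a sensitivity analysis and not as a replacement. With about 20 per arm, dropping the baseline can cost more power than it saves.
4. State the limitation in the protocol and in reports.

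**Cost.** An amendment to the timing of kit hand-out, with no extra stool sample. Samples stay about a month longer at −20 °C in the home freezer unless handed in earlier, and this should apply equally to both groups. The measures for enrolled participants need analysis wording only, with smaller numbers in the placebo-restricted comparison.

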#### Baseline test visit

For both the non-sarcopenic controls and the sarcopenic participants, a test visit at the study center will follow the preparation period. During this visit, the four-day food diary, the IMU and the two frozen fecal samples brought along by the participant (avoiding thawing using ice packs) will be collected and fasted blood samples will be taken.The fecal samples will immediately be stored at -80 °C until analysis of intestinal inflammatory markers (fecal calprotectin, lactoferrin and S100A12) and GM composition. Quantitative Microbiome Profiles (QMP) will be obtained through the following extensive -omics analysis. Targeted (16S/18S) amplicon sequencing analysis of the V3-V4 variable region of the 16S rRNA gene, via reverse polymerase chain reaction (RT-qPCR) technique will provide information about GM taxonomic composition, i.e., the type of GM present, and their abundance.. Metagenomic analysis (comprehensive assessment of DNA of the complete content of a clinical sample) will be performed through whole genome shotgun analysis using next generation platforms. Intestinal inflammatory markers will be determined through Enzyme Linked Immunosorbent Assay (ELISA).In fasted blood samples, the following parameters will be determined: systemic inflammatory parameters (hs-CRP, IL-4, IL-6, IL-13, IL-1β, TNF-α and creatine kinase), muscle markers (myostatin, activin A, irisin, apelin), clinical parameters (hemoglobin, eGFR, serum albumin, fasting glucose, red blood cell count, hematocrit, Mean Corpuscular Volume (MCV), Mean Corpuscular Hemoglobin (MCH), Mean Corpuscular Hemoglobin Concentration (MCHC), white blood cell count and formula, platelet count, hemoglobin A1c (HbA1c), ferritin, aspartate aminotransferase (AST), alanin transaminase (ALT), γ-glutamyltransferase, total and direct bilirubin, total protein, serum protein electrophoresis, uric acid, sedimentation rate, triglycerides and total, high-density lipoprotein (HDL) and low-density lipoprotein (LDL) cholesterol, and hormonal status (25-hydroxyvitamin D, vitamin B12, morning cortisol, insulin, insulin-like growth factor (IGF-1)).

Clinical parameters measured during this visit are the participants’ appendicular lean mass (ALM) by Dual X-Ray-Absorptiometry (DXA) (Horizon A scanner, Hologic Inc., Bedford, MA, USA) in a fasted state. Also, bioelectrical Impedance Analysis (BIA) will be used to assess body composition (Tanita TBF-300, Tanita Coorporation, Tokyo Japan; Omron BF-300, Omron Healthcare Co, Ltd., Kyoto Japan; BodyStat 1500, Bodystat, Isle of Man, UK; Bodystat Quadscan 4000, Bodystat, Isle of Man, UK) in a fasted state. Hand grip strength will be assessed with a hand dynamometer as described above. In the upper dominant leg, flexor and extensor muscle strength will be assessed with isometric (60° and 90°), isotonic (40,20 1 and 60% of individual 1- repetition maximum (1-RM) and isokinetic (60°/s and 180°/s) BIODEX (Biodex system 3 Pro Multijoint System) measurements as previously described by Baggen et al. [39]. Two minutes of rest will be provided between these three BIODEX measurements. Axillary body temperature (Predictor, GEON Corporation, Chang Hwa Hsien, Taiwan) and blood pressure will be determined (Microlife, Microlife AG Swiss Corporation, Widnau Switzerland). Physical performance and balance will be assessed with the Short Physical Performance Battery (SPPB) [40], the Mini-Balance Evaluation System Test (Mini-BESTest) and the gait speed test [41]. Gait speed will be determined over a six-meter distance, only timing the inner four meters. Participants will be requested to walk at their usual pace. Low gait speed is defined at the cut-off of ≤ 0.8 m/s. Furthermore, the physical frailty stage (Fried criteria), activities of daily living (ADL; Barthel index) [42], quality of life (QoL; two questionnaires: 36-Item Short Form Health Questionnaire (SF-36) [43] and SarQoL [44]), number of falls, fall circumstances and fear of falling (Falls Efficacy Scale-International (FES-I) questionnaire [45]) will be evaluated. Cognitive performance will be assessed with the Repeatable Battery for Assessment of Neurological Status (RBANS) (measuring language, visuospatial skills, attention and immediate and delayed memory) [46], the Trail-Making-Test (TMT) [47], the Stroop test and Maze-test [48]. Finally, nutritional status will be assessed with the Mini-Nutritional Assessment-Short Form (MNA-SF) [49]. Participants who successfully complete the study test visit will be offered a gift voucher worth 15 euros.

#### Intervention period

In the longitudinal RCT phase of the TEMPUS-FUGIT study, sarcopenic older adults will be block randomized to one of five interventional programs, stratified according to sex, via a sealed opaque envelope by an independent researcher. Participants in each of the interventional groups will follow a 12-week intervention period as previously described [29]. Briefly, the interventions consist of a training program and/or nutritional supplementation. The exercise intervention comprises an adapted version of the home-based Otago exercise program (OEP) consisting of warming-up, balance, strength and stretching exercises together with a walking program. The OEP has been proven to effectively reduce falls in older community-dwelling adults. Currently the OEP is being investigated in the context of sarcopenia, reporting a preliminary beneficial effect [50, 51]. The protein intervention consists of a personalized amount of protein supplementation, rich in leucine (Resource instant protein, Nestlé), aiming to reach the RDA of 1.5 g/ kg BW/day, spread equally over the day [35]. The placebo protein is isocaloric digestible maltodextrin (Resource dextrin maltose, Nestlé). Omega-3 PUFA supplements consist of 450 mg docosahexanoic acid (DHA) and 500 mg of eicosapentanoic acid (EPA) per day. The omega-3 PUFA placebo contains 1 g peanut oil. All groups receive vitamin D supplementation (800 IU cholecalciferol). Researchers and participants will be blinded to the nutritional supplements, but not to the exercise program. The statistician is blinded to all the interventions. At each contact moment during the intervention, researchers encourage participants to comply to the interventions. An overview of the study design/ intervention groups is given in Fig. 3.

